### Secondary outcomes

Secondary outcomes are differences in change between the intervention and control group from baseline to 6 months for the composite cardiovascular disease risk score, and from baseline to 6 and 12 months for the single CVD risk factors, glycaemic control, bone health, body composition, physical fitness, physical activity, quality of life, mental health, fatigue and adverse events (safety). Additional file 2: Table S1 lists all assessed outcome variables.

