The secondary analyses include several steps: *First*, we will do the same ITT analysis with appropriate means of imputation of missing data for all the secondary outcomes. *Second*, we will perform sensitivity analysis on the primary and all secondary outcomes, including, a) complete data (complete case analysis), i.e. observations with missing information on relevant variables will be dismissed; b) analysis of intermediate effects after 3 and 6 months of intervention; c) dose-response analysis based on the actual physical activities (min of vigorous physical activities per week) or physical performance (VO_2_peak) during the period of interest, independent of the group allocation; and, d) per protocol analysis.

Per protocol analysis will include several analyses based on the actual “treatment” that the participants adhered to (independent of group allocation), first based on the reported compliance and second based on the assumed compliance. In the first analysis based on the *reported compliance*, the following participants will be analysed as being in the “intervention group”: participants randomized into the intervention group who reported in the web-diary to have reached at least 2/3 of the target physical activity (addition of 100 min of moderate to vigorous physical activities [MVPA]); and, participants who were randomized to the control group but reported in the physical activity questionnaires to have increased their physical activity level by more than 30 min of extra MVPA per week during the period of interest. The rest of the participants will be analysed as being a “control”. The second analysis of *reported compliance* will include only the participants sufficiently compliant with the protocol that they were allocated to. It will include those randomized into the intervention group who completed at least 2/3 of training volume (e.g. the addition of 100 min per week of vigorous PA) and compare them to those randomized into the control group with no more than 30 min of extra vigorous PA per week than at baseline during the period of interest.

The analysis on the *assumed compliance* will be done according to the analyses of the reported compliance but with participants being defined as compliant if they reach an increase of ≥5% in VO2peak and/or ≥10% in the ventilatory anaerobic threshold from baseline [135].

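### The compliance-based and dose-response sensitivity analyses extend to adverse events, although an event can itself decide which group a participant is counted in

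*Protocol article*

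**What the plan says.** The Secondary outcomes section ends its list with "quality of life, mental health, fatigue and adverse events (safety"), compared between arms at 6 and 12 months. In Data analysis, the secondary analyses begin with an intention-to-treat analysis of every secondary outcome. Then comes the sentence "we will perform sensitivity analysis on the primary and all secondary outcomes", which covers complete-case, intermediate-time, dose-response and per-protocol analyses. Safety is not excepted.

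On the per-protocol part the plan states: "Per protocol analysis will include several analyses based on the actual" treatment adhered to. It has three elements:

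- **Regrouping by reported compliance.** The exercise group consists of intervention participants "who reported in the web-diary to have reached at least 2/3 of the target physical activity", plus controls who "increased their physical activity level by more than 30 min of extra MVPA per week during the period of interest". For everyone else: "The rest of the participants will be analysed as being a" control.
- **Compliers only.** A second analysis "will include only the participants sufficiently compliant with the protocol that they were allocated to".
- **Assumed compliance.** Both are repeated with "participants being defined as compliant if they reach an increase of ≥5% in VO2peak and/or ≥10% in the ventilatory anaerobic threshold from baseline".

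The dose-response analysis relates outcomes to vigorous activity or VO2peak over the period of interest, ignoring allocation.

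**The concern.** For an efficacy outcome, grouping by compliance is a familiar and arguable trade-off. For adverse events it is worse, because the outcome can cause the group label. A participant hurt while exercising may stop, miss two thirds of the target, and fail to gain fitness. Under regrouping that injury is counted in the comparator; under the compliers-only rule it disappears.

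The filter is also one-sided. An injury tends to take an intervention participant out of the exercise group, whereas an injured control is less likely to exceed 30 extra minutes and so stays a control. Equal cut-offs or instruments in the two arms would not cure this. Dose-response by activity over the whole period has the same fault: injured people log fewer minutes, so more exercise looks safer.

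A sensitivity analysis should test the main result. This one errs in a foreseeable and reassuring direction. The Publication policy places safety endpoints in the main paper, and the Discussion intends to offer the programme to other clinics if it proves effective.

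**Working it through.** **Plan figures that can be reproduced.** Recruitment per arm: 60 / (1 - 0.20) = 75, as stated under Sample size. Compliance threshold: 2/3 of 2.5 h = 2/3 × 150 = 100 min per week, as stated under Data analysis. Neither is in dispute.

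**Assumed inputs.** The protocol gives no event or compliance rates, so these are all assumptions:

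- b, background event risk in both arms: 5%, 10%, 20%
- x, additional exercise-caused injury risk in the intervention arm: 5%, 10%, 20%
- q, non-compliance among intervention participants without an exercise injury: 30%
- c, controls who exceed 30 extra minutes: 20%, given background risk only
- s, probability that an exercise-injured participant falls below target: 25%, 50%, 75%, 100%

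Background events are taken not to affect compliance.

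**Formulas, with equal arms.**

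- As randomised: difference = [x + (1 - x)b] - b = x(1 - b)
- Relabelled exercise group: size = x(1 - s) + (1 - x)(1 - q) + c; events = x(1 - s) + (1 - x)(1 - q)b + cb
- Relabelled comparator: size = xs + (1 - x)q + (1 - c); events = xs + (1 - x)qb + (1 - c)b
- Compliers only: [x(1 - s) + (1 - x)(1 - q)b] / [x(1 - s) + (1 - x)(1 - q)] - b

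**Worked scenario: b = 10%, x = 10%, s = 100%.**

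- As randomised: 19.0% v 10.0%, difference +9.0 points.
- Relabelled exercise group: size 0 + 0.63 + 0.20 = 0.83; events 0 + 0.063 + 0.020 = 0.083; risk 10.0%.
- Relabelled comparator: size 0.10 + 0.27 + 0.80 = 1.17; events 0.10 + 0.027 + 0.080 = 0.207; risk 17.7%. Difference -7.7 points.
- Compliers only: 0.063 / 0.63 = 10.0% v 10.0%, difference 0.

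**Range over all b and x, in percentage points.** The as-randomised difference is +4.0 to +19.0 throughout.

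| Injured who fall below target (s) | Relabelled difference | Compliers-only difference |
|---|---|---|
| 100% | -3.5 to -15.3 | 0 |
| 75% | -1.5 to -6.1 | +1.5 to +7.8 |
| 50% | +0.4 to +2.7 | +2.9 to +14.4 |
| 25% | +2.4 to +11.3 | +4.3 to +20.1 |

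At 25%, injured participants comply more than the uninjured (30% non-compliance). Harm stays visible; the relabelled figure is smaller than the as-randomised one because the groups are mixed.

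**Illustration in counts (assumed), 75 per arm.** Injuries 12 v 6, risk ratio 2.0. In the intervention arm 44 of 63 uninjured and 3 of 12 injured meet the target; in the control arm 14 of 69 uninjured and 1 of 6 injured exceed 30 min.

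- Relabelled: (3 + 1)/(44 + 3 + 14 + 1) = 4/62 = 6.5% v (9 + 5)/(150 - 62) = 14/88 = 15.9%, risk ratio 0.41.
- Compliers only: 3/47 = 6.4% v 5/60 = 8.3%, risk ratio 0.77.
- If 4 of 12 injured meet the target, compliers only is 4/48 v 5/60, ratio 1.00; with 5 it is 5/49 v 5/60, ratio 1.22.
- If 7 of 12 meet it, relabelled is 8/66 = 12.1% v 10/84 = 11.9%, and the reversal is gone.

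**The case against.** The strongest reply is that the plan already contains the right analysis. The intention-to-treat step comes first and covers all secondary outcomes, so adverse events will be compared by randomised arm. Under Adverse events, every event is recorded whether or not related to exercise, serious events are reported, and an independent auditor monitors safety. This stands, and it limits the point to the sensitivity analyses.

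A reader might infer more than the text supports:

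- *That the trial's safety result as a whole is hidden or reversed.* The as-randomised comparison rules this out.
- *That the complete-case analysis also drops injured participants.* That rule dismisses observations with missing data. Stopping training is not missing data, and the plan tries to follow everyone randomised, including those who leave the allocated treatment.
- *That events are forced into a change-from-baseline analysis with imputation.* The Secondary outcomes sentence is a collective one. Model selection allows logistic, Cox or Poisson regression by type of endpoint, and the plan asks only for appropriate imputation.

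It can also be said that the size is conditional. That is right: a brief or late injury may leave a participant above target, the relabelled reversal needs injured participants to comply much less than uninjured ones, and the compliers-only reversal in the count example hangs on one participant. Finally, relating events to actual exercise is a legitimate safety question. That also stands, provided exposure is measured before the event.

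**Conclusion.** The point holds for the per-protocol analyses (reported and assumed compliance) and for dose-response by whole-period activity. As written, they apply to adverse events, and the event can determine the grouping or the dose.

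The direction follows from the plan's own rules, on the condition that injury reduces compliance; the size does not, because every rate used is an assumption. With 30% non-compliance among the uninjured, the relabelled analysis reverses the sign if 75% or more of the injured fall below target and shows almost nothing at 50%. The compliers-only difference is zero at 100% and reduced but positive at 75%. If injured participants comply about as well as the rest, harm remains visible. The wording should be corrected, but the main safety comparison is not at risk.

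**What to change.** Add one sentence to the secondary analyses in Data analysis: adverse events are exempt from the compliance-based regrouping and compliers-only analyses, for both reported and assumed compliance, and the safety analysis is the comparison by randomised arm in all randomised participants. If events are also related to exercise exposure, state that each event is attributed to the activity level at or before its onset, not to compliance over the whole period.

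The cost is that one sentence and fewer exploratory safety analyses. No data collection, visit or clinical rule changes. An onset-based exposure analysis would have daily diary data in the intervention arm but only visit reports (months 3, 6 and 12) and the periodic device measurements in controls, so it would be coarser there.

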### Study population / inclusion criteria

Eligible participants are identified by the Swiss Childhood Cancer Registry (SCCR) [40, 41]. SURfit includes CCS aged <16 years at diagnosis, diagnosed with a cancer classifiable according to the International Classification of Childhood Cancer (ICCC-3) [42] or Langerhans Cell Histiocytosis, who were diagnosed and treated at a clinic of the Swiss Paediatric Oncology Group (SPOG), survived ≥5 years since primary cancer diagnosis or any subsequent cancer event (relapse or 2nd tumour), and, are aged ≥16 years at baseline (T0a) of the study. Participants have to agree that they will commit to the conditions of their study group allocation prior to the allocation and independent of the allocation.

The presence of any of the following criteria, assessed at baseline (T0a), leads to exclusion of the participant: participation in another clinical trial, inability to exercise or exercise potentially harmful, pregnant or breast feeding, cardiac arrhythmias under exercise, diagnosis of diabetes <3 months previously, detection or presence of a clinical condition that needs immediate treatment, planned surgeries within the subsequent 12 months that interfere with physical exercising, major musculoskeletal injuries/fractures <2 months previously, change in medication that interfere with the parameters of the CVD risk score < 1 month previously, >4 h of reported vigorous physical activities per week, or, inability to follow the procedures and understand the intervention and assessments of the study, e.g. due to cognitive impairment, language problems, or psychological disorders.

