#### Physical activity intervention (intervention group)

Survivors in the intervention group are asked to add at least 2.5 h of intense physical activities per week. These should include 30 min of strength building exercises and 2 h of aerobic exercises per week. Exercise bouts lasting 20 min or longer are counted towards the total weekly training time. This “dose” of physical activity is based on the international recommendations of healthy physical activities from the Centre of Disease Control and Prevention (CDC; www.cdc.gov) [133].

Based on the initial exercise test, general health status and participant’s preferences and motivation, subjects of the intervention group receive a counselling at the second visit of the baseline assessment (T0b; Fig. 1
**,** Additional file 2: Table S1). A standardized approach is used to assess survivors’ preferences with respect to physical activities, identify possible barriers and determine the individual motivation to start specific activities. Based on this assessment, individualized physical activities are defined and implemented into the participant’s daily life. Survivors of the intervention group are also motivated to incorporate activities of moderate intensities into daily life such as walking instead of driving or climbing stairs instead of taking the escalator. Participants are also advised to reduce inactive behaviour such as television viewing, computer games, etc. with the aim of reducing 25% of their actual media time. The motivational interview is performed by one of the project physiotherapists who have been trained prior to the study.

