#### Data analysis

Descriptive statistics will be used for clinical, sociodemographic and prognostic variables measured at baseline (stratified by intervention and control group). We will use frequencies and proportions with 95% confidence intervals (CI) for categorical variables and mean with ±SD or 95% CI (or median and range) for continuous variables. Descriptive analysis of baseline characteristics will be performed as soon as the baseline assessments are completed for all participants. This cross-sectional analysis will inform about the comparability of the treatment groups and the need for adjustment of between treatment group comparisons. Furthermore, baseline assessments will provide important results about characteristics, health behaviours and health status of long-term CCS in Switzerland. We will also compare the distribution of baseline sociodemographic characteristics to the Swiss Childhood Cancer Registry, to estimate the representativeness of our sample.

The primary analysis will be conducted as intention-to-treat analysis (ITT) for the primary outcome (change in composite CVD score from T0 to T12). All participants will be analysed in the group where they were originally allocated and missing data will be imputed by means of last observation carried forward (LOCF) [134]. LOCF is an appropriate procedure in this setting because it will lead to more conservative effect estimates (i.e. towards the null), because lost to follow-up is more likely to occur in the intervention group (because of an intensive and time-consuming programme) which is the group expected to change (improve). Attempt will be done to follow up all randomised participants, even if they withdraw from the allocated treatment. If the parameters of the composite CVD risk score are skewed, they will be transformed to reach normal distribution for calculating the z-scores.

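### The dose-response analysis takes the level of vigorous activity as the dose for outcomes that are changes from T0, so its slope mixes habitual with added activity and is probably diluted

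*Protocol article*

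**What the plan says.** All references are to the protocol article.

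- **Dose.** Under Data analysis, item (c) of the sensitivity analyses is a "dose-response analysis based on the actual physical activities (min of vigorous physical activities per week) or physical performance" (VO2peak). The dose is taken "during the period of interest, independent of the group allocation".
- **Outcomes covered.** The list opens with "we will perform sensitivity analysis on the primary and all secondary outcomes". The primary outcome is the "change in composite CVD score from T0 to T12". Secondary outcomes defines the others as differences in change as well.
- **Intervention.** "Survivors in the intervention group are asked to add at least 2.5 h of intense physical activities per week". The Control group section asks controls to hold their level constant and states the aim as testing additional activity.
- **Entry.** Study population / inclusion criteria excludes ">4 h of reported vigorous physical activities per week", so 0 to 240 min per week is admissible.
- **Per-protocol rules.** In the same section these refer to added activity, for example controls with "no more than 30 min of extra vigorous PA per week than at baseline", or to a rise in VO2peak from T0.
- **Adjustment.** The model selection paragraph says that models may also be adjusted for baseline values and prognostic factors if these are unequally distributed between the arms. Baseline activity is not named; health behaviours are, under the same condition.

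**The concern.** The dose and the outcome are on different footings. The outcome is a change and the treatment is an increment, but the dose is a total that contains whatever the person was doing before T0. A control who stays at 240 min, as instructed, is placed 90 min above an intervention participant who moves from 0 to 150 min. If added activity is what moves the outcome, the first should show no effect and the second the full effect of the target, yet the regression ranks them the other way round.

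The Compliance section names dose-response analysis as one purpose of the activity measurements, so a slope will probably be reported. As written, a real relation between added activity and improvement could be reported as weak or absent. A reader could not tell whether the slope reflects adding activity or having been active all along.

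**Working it through.** **Plan figures.** The article gives no figure for the dose-response analysis, so there is none to reproduce. The simulations use its 60 complete cases per arm. The stated inflation for 20% loss reproduces: 60 / (1 - 0.20) = 75 per arm.

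**Formula.** Let B be vigorous minutes per week at T0, D the change, and L = B + D the level during follow-up. If change in outcome = β × D, regressing it on L alone gives an expected slope of

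β × [Var(D) + Cov(B,D)] / [Var(B) + Var(D) + 2 Cov(B,D)].

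With equal SDs for B and D this is exactly 0.5 β, whatever their correlation.

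**Numbers in the formula.** The article gives no SDs or correlations, so all of these are assumed.

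| SD(B) | SD(D) | corr | Slope / true slope |
|---|---|---|---|
| 69 (uniform on 0-240) | 95 | 0 | 9025 / 13786 = 0.65 |
| 69 | 60 | -0.6 | 1116 / 3393 = 0.33 |
| 30 | 80 | -0.6 | 4960 / 4420 = 1.12 |

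Over SD(B) 30 to 69, SD(D) 60 to 95 and correlations -0.6 to 0.3, the ratio runs from 0.33 to 1.12. It exceeds 1 only when corr(B,D) is below -SD(B)/SD(D).

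**Simulation.** 60 per arm, 800 runs per scenario, T0 activity uniform or right-skewed on 0 to 240 min. Mean added activity was 75, 100 or 150 min (SD 75) in the intervention arm and 0 (SD 40) in controls. There was no measurement error.

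| Dose in the model | Slope / true slope |
|---|---|
| Level only, change unrelated to T0 activity | 0.50 to 0.71 |
| Level only, active people add less | 0.53 to 0.97 |
| Level plus T0 activity, or change from T0 | 0.98 to 1.01 |

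**If T0 activity itself relates to the later change.** Here T0 activity was uniform, 150 min were added on average and β was -0.2 per 100 min. Each 100 min of T0 activity was also given its own effect on the change in risk.

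- Effect +0.1 (active people improve less): level-only ratio 0.48.
- Effect -0.1, -0.2 and -0.3 (active people improve more): 0.83, 1.00 and 1.18.
- Level plus T0 activity stays at 0.99 to 1.01 throughout.
- Change without T0 activity as covariate fell to 0.85 and 0.77 for effects -0.2 and -0.3 when active people also added less. A bare change score is therefore not enough.

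**Measurement error.** Take SD(B) = 69, SD(D) = 73, zero correlation, and independent error of variance e² at each visit. T0 reliability is λ = Var(B) / (Var(B) + e²). The ratios to β are:

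- level only: Var(D) / (Var(B) + Var(D) + e²)
- bare change: Var(D) / (Var(D) + 2e²)
- level or change with T0 activity as covariate: Var(D) / (Var(D) + e² + (1 - λ) Var(B))

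With Var(B) = 4761 and Var(D) = 5329:

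| Assumed λ | e² | Level only | Bare change | With T0 covariate |
|---|---|---|---|---|
| 0.70 | 2040 | 0.44 | 0.57 | 5329 / 8798 = 0.61 |
| 0.65² = 0.42 | 6508 | 0.32 | 0.29 | 5329 / 14586 = 0.37 |

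The second row reads the 0.65 validity correlation in the Accelerometer section as pure independent error, which is pessimistic: stable person-specific error would cancel in a change.

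**The case against.** **Item (c) is one clause in a condensed article.** It names the exposure but gives no model, and covariates are commonly left to the analysis plan. A level with T0 activity as covariate, or a repeated-measures model, would be compatible with the text. This stands in part: the article does not rule out adjustment. But the clause does fix a dose in stated units. The only adjustment rule that the article gives is optional and depends on imbalance between arms. The arms could be perfectly balanced on T0 activity and the pooled slope would still be affected.

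**A level can be a legitimate dose.** Activity continued through the year may shape that year's course, and the Accelerometer section cites an absolute daily impact level as effective for bone. This stands as a reason not to claim that prior activity is irrelevant to every outcome. It also favours entering level and T0 activity together, so that the two can be separated.

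**The direction is not certain.** A reader might infer that the slope must be biased towards zero. The document does not support that: the ratio reaches 1 or more under a strong negative correlation between T0 activity and change, or if active people improve more.

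**A change score is noisy, and noise attenuates.** This stands. Under heavy independent error a bare change does no better than the level (0.29 against 0.32). With T0 activity as covariate the result is better in both rows, but still well short of 1.

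**Change in VO2peak is circular for the primary outcome.** This stands: according to Primary outcome, cardiorespiratory fitness is one component of the composite score.

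**The stakes are limited.** This also stands. The analysis is one of four listed sensitivity analyses, and the 240 against 150 min comparison is an extreme case.

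**Conclusion.** The point holds as a mismatch between dose and outcome. Followed as written, item (c) gives a slope that mixes habitual with added activity, out of step with the intervention, the control contrast and the per-protocol rules of the same article.

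Dilution is the likely result, to about 0.5 to 0.97 of the true slope in the main simulated scenarios. That range is illustrative and not a bound. It assumes that change in activity drives change in outcome, that T0 activity is left out of the model, and that activity is measured without error. The SDs and correlations are assumed, and other plausible values give ratios from 0.33 to 1.18. The uncertain sign does not defend the plan, since a slope of unknown bias cannot be read as a dose-response.

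A reader might also infer that the trial's main result is at risk. It is not: the primary intention-to-treat comparison and the sample size do not use this dose.

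**What to change.** For analysis (c), state that every model includes T0 vigorous activity, measured with the same instrument in both arms, and the T0 value of the outcome, alongside follow-up activity. Equivalently, use change from T0 in min per week with T0 activity and the T0 outcome as covariates. Make this unconditional, not dependent on imbalance between arms.

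Where VO2peak is kept as a dose, enter its T0 value in the same way. Do not use it as a dose for the composite CVD score unless the fitness component is removed from the score for that analysis.

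The cost is a sentence or two in the analysis plan. No new data are needed, because the accelerometer is worn at T0, T6 and T12. The price is wider intervals, and some attenuation from error in measured activity will remain; the report should say so.

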For motivational reasons each survivor of the intervention group is equipped with a step counter (pedometer, Model Fitbug Air) and asked to document daily steps. Participants keep a daily training log using a web-based platform with individual anonymous logins. Data on 1) strenuous exercise performed that day (type of exercise, duration), 2) step counts (overall and aerobic steps), 3) media-related sedentary time and sleeping hours, and 4) mood and well-being are entered and graphically displayed to give the participants an immediate feedback about their progress. The participants receive a “reminder” message on his or her mobile phone or via email if no entries are made for three consecutive days. If there are no entries for a whole week, the survivor is contacted by phone by his “personal coach” (physiotherapist). There are also scheduled phone contacts after 1, 2, 4, 5, 8 and 10 months of the intervention to discuss compliance, motivation, and progress and to re-counsel the survivors on their training plan. Training logs and physical activity behaviour are checked and discussed during the clinic visits (at months 3 and 6), and exercise counselling is repeated.

After the 1-year assessment, participants of the intervention group can keep their step counters and will still have access to the web-based training log to report and view their activity data, but no further support is given from the research team. A follow-up after 1–2 years off trial is planned but this is not subject of the current study protocol.

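### The two-thirds compliance threshold uses MVPA in one reported-compliance analysis and vigorous activity in the other, and the diary named for the first shows by itself neither added minutes nor MVPA

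*Protocol article*

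**What the plan says.** All references are to the Protocol article.

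- **Assigned activity** (Physical activity intervention). Intervention participants are "asked to add at least 2.5 h of intense physical activities per week". On its make-up: "These should include 30 min of strength building exercises and 2 h of aerobic exercises per week". The same section separately encourages moderate everyday activity such as walking and using stairs.
- **First reported-compliance analysis** (Data analysis). Intervention participants count as treated if they "reported in the web-diary to have reached at least 2/3 of the target physical activity (addition of 100 min of moderate to vigorous" activity). Controls are moved to the treated group if they "reported in the physical activity questionnaires to have increased their physical activity level by more than 30 min of extra MVPA per week".
- **Second reported-compliance analysis** (Data analysis). Intervention participants are kept if they "completed at least 2/3 of training volume (e.g. the addition of 100 min per week of vigorous PA"). They are compared with controls whose vigorous activity rose by no more than 30 minutes per week over baseline. No instrument is named.
- **The diary** (Physical activity intervention). Its content is listed as "Data on 1) strenuous exercise performed that day (type of exercise, duration), 2) step counts", then media time and sleep, then mood and well-being. It is described for the intervention group. The Control group section gives controls access only after the study year.
- **Entry limit** (Study population / inclusion criteria). The activity-related exclusion is ">4 h of reported vigorous physical activities per week".

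**The concern.** The per-protocol analyses are planned for the primary and all secondary outcomes, and the threshold decides who counts as treated. Two things do not fit together.

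First, the two reported-compliance analyses both claim to apply two thirds of the assigned activity, yet measure it in different intensity bands. They can classify the same person differently, and the reader could not tell whether a difference in results comes from the analysis design or from the change of band.

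Second, the first analysis asks for an addition of MVPA and names a source that records daily totals of strenuous exercise. An addition needs a baseline, and none is named for the intervention arm. Strenuous exercise is also not the same quantity as MVPA.

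The likely consequence is misclassification of treatment received. If unchanged, already active participants were counted as treated, the estimated effect would be expected to move towards no effect. The article gives no figures from which to size this.

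**Working it through.** **1. The threshold itself.** Target: 2.5 h × 60 = 150 min per week. Components: 30 + 120 = 150 min. Two thirds: 2/3 × 150 = 100 min per week. The plan's figure reproduces. The first definition omits the words per week, but the arithmetic shows that a weekly figure is meant.

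**2. Intensity.** Apply both definitions to the same added weekly minutes:

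| Added moderate | Added vigorous | First (MVPA ≥ 100) | Second (vigorous ≥ 100) |
|---|---|---|---|
| 0 | 100 | met | met |
| 50 | 50 | met | not met |
| 100 | 0 | met | not met |

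The switch also affects controls. One who adds 40 min of moderate activity and no vigorous activity exceeds the 30-min MVPA limit and is analysed as treated in the first analysis. In the second, the same person stays a compliant control.

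**3. What the diary can show.** Let B be habitual weekly minutes before the intervention, A the minutes added, and D the diary total. Then D = B + A, so A = D − B, and the diary alone gives only D. If D were compared directly with 100, the addition needed to pass would be max(0, 100 − B). A true addition of 100 needs D = B + 100. The entry limit allows B up to 4 × 60 = 240 min of vigorous activity.

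| B (min/week) | Addition needed if D alone is compared with 100 | D needed for a true addition of 100 |
|---|---|---|
| 0 | 100 | 100 |
| 60 | 40 | 160 |
| 100 | 0 | 200 |
| 150 | 0 | 250 |
| 240 | 0 | 340 |

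For every B from 100 to 240, nothing need be added. The B values are illustrative because the article gives no baseline distribution. The table treats reported vigorous activity and the diary's strenuous exercise as the same quantity.

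**4. MVPA from the diary.** The listed exercise field covers strenuous exercise. The other activity field is step counts, which are not minutes of MVPA. No field for minutes of moderate activity is described.

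**The case against.** The strongest reply is that both definitions say addition. Someone who keeps 200 min per week and adds nothing fails both as worded. That is correct. A reader might infer that the plan will count such people as compliant, but the text does not say so. It would happen only if diary totals were used without subtracting a baseline.

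Baseline information is also within reach. Activity is measured by accelerometer between the T0 visits, vigorous activity is assessed for eligibility, and a seven-day recall is among the instruments. A condensed article may leave the choice of baseline to a fuller document. This weakens the concern, but the article does name a source for the first analysis, and that source does not deliver the stated quantity.

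Three further inferences should not be drawn:

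- The diary problem need not extend to the second analysis, which names no instrument.
- The rule that "Exercise bouts lasting 20 min or longer are counted towards the total weekly training time" is not shown to have been dropped. The reference to training volume in the second definition can be read as including it.
- The number of people with a baseline of at least 100 min is not the number misclassified, since active participants may also add the full amount. No percentage can be supported.

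The second definition's 100 min is introduced as an example, which softens the conflict but leaves vigorous as the only band given there. The control limit in that analysis is also in vigorous minutes. Finally, the plan includes a dose-response analysis and an assumed-compliance analysis based on fitness change from baseline, so these results would not stand alone.

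**Conclusion.** The point holds as an inconsistency in the secondary reported-compliance analyses and should be corrected. The difference between MVPA and vigorous activity is on the face of the text and needs no assumption. It changes who is classed as treated in both arms.

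The mismatch between the diary and the first definition also holds: taken alone, the diary as described yields neither an addition nor MVPA. This rests on the listed fields and on the inference that the diary starts with the counselling at T0b; the supplementary visit table is not shown. Misclassification of participants already doing 100 to 240 min per week is possible, not certain, and its extent is unknown.

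The intention-to-treat primary analysis is not affected.

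**What to change.** Reconcile the intervention description, the diary description and the Data analysis section:

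1. Use one intensity band in both reported-compliance analyses, consistent with the assigned activity, and have the sponsor state how intense maps onto that band. Report the other band as a labelled sensitivity analysis.
2. Define added minutes in both arms as the change from T0 in weekly minutes on the same instrument. The Seven-Day Physical Activity Recall or the activity questionnaire would serve. The recall separates moderate, hard and very hard activity, and both groups report activities at T3, T6 and T12.
3. Keep the diary as supporting information on adherence between visits.

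The cost is a change of wording and some extra analysis. No new data are needed, provided the supplementary visit table confirms that the chosen questionnaire is completed at T0. There are two downsides: fewer participants may be classed as compliant, and a seven-day recall samples only the week before each visit, whereas the diary runs daily.
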